## Abstract

**Background:**

Burns and related procedures are painful and distressing for children, exposing them to acute and chronic sequelae that can negatively affect their physiological, psychological, and social functions. Non-pharmacological interventions such as distraction techniques are beneficial adjuncts to pharmacological agents for procedural pain, state anxiety, and itch in children with burns but have limitations (e.g. lack of research on burn-related itch, tailoring, and consensus on optimal treatment). Hypnotherapy is a non-pharmacological intervention that can be tailored for varied settings and populations with evidence of benefit for itch and superior effectiveness in comparison to other non-pharmacological interventions for children’s procedural pain and state anxiety. Thus, children with burns can benefit from hypnotherapy as an adjunct to pharmacological agents. Yet, in paediatric burns, rigorous studies of effectiveness are limited and no studies have been identified that screen for hypnotic suggestibility, an important predictor of hypnotherapy outcomes. Considering potential barriers to the delivery of hypnotherapy in paediatric burns, the proposed study will examine the feasibility and acceptability of hypnotic suggestibility screening followed by hypnotherapy for procedural pain, state anxiety, and itch in children with acute burns.

**Methods:**

An observational mixed-methods feasibility and acceptability study will be conducted over 15 weeks. Eligible children (*N* = 30) aged 4 to 16 years presenting to a paediatric burns outpatient centre in a metropolitan children’s hospital in Australia with acute burns requiring dressing changes will be included. Eligible parents of children (*N* = up to 30) and clinicians who perform dressing changes (*N* = up to 20) will also be included. Child participants screened as having medium to high suggestibility as assessed by behavioural measures will receive hypnotherapy during dressing changes. A process evaluation will target feasibility and acceptability as primary outcomes and implementation (i.e. fidelity in delivery), reach, potential effectiveness, and adoption of evaluation procedures and intervention as secondary outcomes.

**Discussion:**

Ethical approval was obtained from the Queensland Children’s Hospital and Health Service ethics committee. Results will be published in peer-reviewed publications and conference proceedings.

The findings will guide the design of future trials on the effectiveness of hypnotherapy and inform the development of child-centred hypnotic interventions in children with burns.

**Trial registration:**

Australian New Zealand Clinical Trials Registry ACTRN12620000988954

**Supplementary Information:**

The online version contains supplementary material available at 10.1186/s40814-022-01017-z.

## Background

Acute paediatric burns pose a major problem to the health of children affecting yearly more than half a million persons below the age of 20, one-quarter of whom are below the age of 16 years [1]. Burns and concomitant treatments can cause pain, anxiety, and itch for children [2]. In the acute phase of treatment, pain, anxiety, and itch can aggravate each other, increase the inflammatory response, reduce adherence to treatment, and prolong the recovery process [2]. In turn, subsequent relapse and/or delayed recovery can lengthen hospitalisation time, augment medication requirements, and inflate healthcare costs [2]. Furthermore, inadequately treated pain, anxiety, and itch elicited by burns and related procedures can cause chronic sensory alterations (e.g. hyperalgesia, persistent pain) and psychosocial sequelae (e.g. psychopathologies; social, schooling, and sleep problems) [2]. These sequelae can increase the need for medications during subsequent procedures and may have a devastating effect on children’s well-being and quality of life. Treating post-burn itch, procedural pain, and state anxiety can prevent related biopsychosocial sequelae (e.g. post-traumatic stress disorder) and the impact of these sequelae on families as well as enhance re-epithelisation [2].

Procedural pain, state anxiety, and itch are usually treated in children with burns using non-pharmacological and pharmacological interventions [3]. According to a review of systematic reviews, hypnotherapy and distraction are supported by the most robust evidence of efficacy for paediatric procedural pain and distress in comparison to other non-pharmacological interventions [4]. Distraction techniques are among the most investigated and popular non-pharmacological interventions in paediatric burns [3]. Yet, evidence regarding distraction techniques is lacking for burn-related itch [5]. Plus, the high cost of virtual reality or multimodal devices, the need for training and technical support, and the lack of tailoring and consensus on the optimal method of delivery and technology may limit the use of distraction techniques [6, 7].

Hypnotherapy has a long history of use in the treatment of children’s physical and psychological problems [8]. A recent systematic review and meta-analysis showed that hypnotherapy can be effective in targeting both the affective and sensory components (i.e. situational determinants) of pain [9]. Neurophysiological studies have indicated that the effects of hypnotherapy on pain intensity and unpleasantness are via modulating the activity in the anterior cingulate cortex and increasing connectivity between cortical and subcortical areas [10]. Hypnotherapy may also be beneficial for treating burn-related itch as well as itch-related cognitive and emotional consequences, including distress, discomfort from itching skin, and scratching habits [11]. Although research has been predominantly conducted in adults, hypnotherapy may be more beneficial for children due to characteristics that make them more receptive to suggestions (higher suggestibility, fantasy proneness, engagement in play, and motivation to learn new skills) [8]. Systematic reviews indicate that hypnotherapy can be effective and potentially superior to standard care, control conditions, and other non-pharmacological interventions (e.g. distraction) in decreasing children’s procedural pain and state anxiety across a range of conditions [7, 12, 13]. A meta-analysis on hypnotherapy for procedural distress found larger effect sizes in children than adults adding to the potential importance of investigating hypnotherapy in children [12].

Hypnotherapy can be easily adapted to diverse settings and tailored to children’s different cognitive levels, preferences, and characteristics [14]. Due to adaptability and minimal technical requirements, hypnotherapy can be delivered within a short period (e.g. 15 min), without a hypnotherapist (self-hypnosis), and in varied delivery modes (live or pre-recorded) [14]. Yet, the delivery and outcomes of hypnotherapy may be influenced by potential barriers related to the paediatric burns setting (distressing nature, short time available to prepare children for medical procedures, possible interruptions), clinicians, and parents [14, 15]. For instance, mixed opinions among clinicians and misconceptions regarding hypnotherapy have been identified in the general population including Australia [14, 16]. Due to the unique biopsychosocial impact of burns, pain elicited by burns and related procedures may adversely affect children’s attitude and compliance and thus the applicability of delivering hypnotherapy and treatment outcomes [2, 15, 17]. Thus, investigating the feasibility and acceptability of hypnotherapy is paramount to guide research and clinical practice in children with burns [14].

Although research has indicated the benefits of hypnotherapy for children with a range of conditions, data is limited in paediatric burns. Only one recently conducted randomised controlled trial (RCT) on hypnotherapy for pain and anxiety in children with burns has been identified in a recent systematic review [6]. The RCT involving some of the current authors indicated that parents of children with acute burns expressed more satisfaction with hypnotherapy in comparison to standard care at the 3rd dressing change [18]. This finding parallels a meta-analysis in adults undergoing medical procedures or surgery in which shorter hospital stays, fewer medication requirements, and greater patient satisfaction leading to more cost-savings were linked to a hypnotherapy intervention delivered by clinicians [19]. Despite evidence supporting hypnotic suggestibility (i.e. degree of responding to hypnotic suggestions) as a predictor of hypnotherapy’s pain and anxiety outcomes in children, feasibility data on hypnotic suggestibility screening are lacking in children with burns [20]. Before investigating the efficacy of hypnotherapy in children with burns further, it is important to investigate the feasibility and acceptability of the intervention in an acute study setting.

## Methods

Reporting and methodology for the proposed study follow the Standard Protocol Items Recommendations for Interventional Trials (SPIRIT 2013) [21], Standards for Reporting Implementation Studies initiative (StaRI) [22], as well as Consolidated Standards of Reporting Trials (CONSORT) - extension to randomised pilot and feasibility trials [23], and Strengthening the Reporting of Observational Studies in Epidemiology (STROBE) [24] (supplementary file 1). The intervention has been reported using the Template for Intervention Description and Replication (TIDieR) [25].

### Study aims and objectives

The primary aims are to investigate the feasibility and acceptability of the intervention (i.e. pre-hypnosis interview, hypnotic suggestibility screening, and hypnotherapeutic session) and evaluation procedures (i.e. recruitment and health outcome data collection). Additionally, the reach, adoption, potential effectiveness, and implementation (i.e. fidelity) of the intervention and evaluation procedures will be examined as secondary outcomes.

### Patient and public involvement

Patients or the public were not directly involved in the study development. A previous study of hypnotherapy involving children with burns and their parents was used to inform the study design [18].

### Design

The study will be conducted using an observational mixed-methods design integrating multiple data sources (clinicians, parents, and children) and data collection methods (quantitative and qualitative) [26]. The use of different perspectives and methods is intended to avoid biases generated by relying on one source of evidence or type of data (e.g. quantitative or qualitative alone). The key outcomes are acceptability (i.e. the extent to which procedures are perceived as fit, satisfying, and appealing, based on experienced affective and cognitive reactions) [27], implementation (i.e. fidelity or the extent to which procedures are delivered as intended), and feasibility (i.e. the extent to which procedures are successfully delivered in a distinctive context that is not fully controlled) [28]. The Theoretical Framework of Acceptability (TFA) [27], Outcomes for Implementation Research [28], and the Reach, Effectiveness, Adoption, Implementation and Maintenance (RE-AIM) framework were used to guide the process evaluation [29–31] (Table 1).

**Table 1 Tab1:** Evaluation frameworks guiding the process evaluation and data collection

Evaluation framework	Implementation outcome	Definition		Data collection	
				Source	Type
RE-AIM [30, 31]	Reach^a^	Willingness of eligible families to participate in the study		Report on the rate of approached eligible families who consent to participate	Quantitative
	Effectiveness	Extent to which the intervention eliciting intended effects and the overall perceived benefits and potential undesired effects		Numeric ratings of pain, anxiety, and itch; physiologic measures of distress; data on wound re-epithelialisation	Quantitative
				Reported adverse events	Qualitative
				Reported perceived benefits	Qualitative
	Adoption by clinicians^b^	Willingness of clinicians to take part in the study		Report on the rate of clinicians conducting dressing changes who consent to join the study	Quantitative
	Implementation	The quality of delivery and consistent delivery of study procedures as intended or prescribed in the protocol (i.e. fidelity)		Report on retention rates among children	Quantitative
				Level of adherence to the fidelity checklist in delivering the intervention	Quantitative
				Completeness of collected data on health outcomes	Quantitative
				Additional adaptations and modifications	Qualitative
	Maintenance	Degree of long-term outcomes by participants or program sustainability within the setting		Not assessed due to the absence of follow-up	
TFA [27]	Acceptability	Perceived self-efficacy	Confidence in the ability to accomplish the behaviour(s) needed to participate in the intervention	Level of children’s perceived self-efficacy on a Likert scale	Quantitative
		Ethicality	Level of understanding of the intervention	Level of children’s positive therapy expectations on a Likert scale	Quantitative
		Coherence	Degree to which the intervention fits well with participants’ beliefs and value system	Semi-structured interview on beliefs and views of children and parents on hypnotherapy	Qualitative
		Perceived effectiveness	The degree to which the intervention is perceived as likely to succeed in its purpose	Families’ and clinicians’ satisfaction with hypnotherapeutic sessions and study procedures (procedures are not rated by clinicians) on NRS	Quantitative
				Semi-structured interview with parents, children, and clinicians on likes, dislikes, and recommendations	Qualitative
		Perceived burden	Perceived extent of effort required to engage in the intervention	Semi-structured interview on perceived required time and cognitive effort for the intervention	Qualitative
OIR [28]	Feasibility	The extent to which study procedures can be successfully delivered to participants in a distinctive context that is not fully controlled		- Number of disruptions - Available time (recordings)	Quantitative
				Field notes on the adequacy of resources	Qualitative

*TFA* Theoretical framework of acceptability, *NRS* Numeric Rating Scale, *OIR* Outcomes for implementation research

^a^*Representativeness* (i.e. the similarity between participants and eligible patients) will not be assessed as part of *Reach* due to the small sample size [31]

^b^Adoption at setting level is already established

### Setting

The study will be conducted in a specialist paediatric burns centre in a metropolitan children’s hospital in Australia.

### Participants

Children presenting to the study setting with acute burns requiring dressing changes, who agree with their parents to be contacted for research, will be recruited after reviewing their medical files and assessing their eligibility as advised by clinicians. Eligible children will be included with their parents and clinicians if they agree to participate. Children’s participation involves providing data and engaging in the intervention. Parents’ participation involves providing proxy-completed outcome data for children under 8 years and acceptability data. Clinicians’ participation involves rating their satisfaction with hypnotherapeutic sessions, reporting adverse events, and advising researchers on eligible families who agree to be contacted for research.

#### Sample size

A formal sample size calculation is not required for feasibility studies [32]. Hypnotherapy will be conducted with 30 children over 15 weeks. The sample size is estimated based on clinic data in the study setting indicating that at least five potentially eligible children present with acute burns each week. Considering a non-participation rate of 15% of the potentially eligible children and the exclusion of 15% of children with low hypnotic suggestibility, it is estimated that 15 weeks will be required to recruit at least 30 eligible children. This number of participants is estimated to be adequate to generate enough information on the feasibility and acceptability of the intervention and study procedures. Participants will be followed up for approximately 5 weeks as the average number of dressing changes is five (one dressing change per week). The participation rate and recruitment time will inform sample size calculations in future studies.

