### Procedures

#### Recruitment

Children presenting to the specialist burns centre for their first burns dressing change and their parents will be screened for eligibility after consulting with clinicians regarding children’s potential eligibility. It is anticipated that approximately three children per week will be recruited (total recruitment period 15 weeks).

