### Study timeline

The study will commence in March 2022 and is expected to be conducted over 15 weeks as shown in the flow diagram (Fig. 1). Enrolment will remain open until July 2022.

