#### Progression criteria

To proceed with investigating the efficacy of hypnotherapy in children with burns, at least the following criteria should be met: sufficient time to deliver the intervention in > 80% of children who commence hypnotherapy; > 50% of families with moderate to high satisfaction rate; recruitment and study completion rates > 50%; collection of > 50% of data across all time points; hypnotherapist adherence to > 50% of intervention elements in the fidelity checklist with > 50% of children; and the absence of serious side effects. The progression criteria cover components of all of the implementation outcomes (Data Synthesis, page 19, above).

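### The recruitment estimate does not follow from its own inputs: they give 30 children in about 8 to 9 weeks, not 15, and 15 weeks is used both for recruitment and for the whole study

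*Protocol article*

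**What the plan says.** The Sample size section of the protocol article gives three inputs:

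- a flow of children: "at least five potentially eligible children present with acute burns each week";
- "a non-participation rate of 15% of the potentially eligible children";
- "the exclusion of 15% of children with low hypnotic suggestibility".

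From these it concludes that "it is estimated that 15 weeks will be required to recruit at least 30 eligible children". The same section makes clear that the 30 are children who receive hypnotherapy, so they are counted after suggestibility screening. It adds: "Participants will be followed up for approximately 5 weeks".

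The Recruitment section expects that "approximately three children per week will be recruited (total recruitment period 15 weeks"). The Study timeline section says that the study, starting in March 2022, "is expected to be conducted over 15 weeks", and that enrolment stays open until July 2022. The Methods paragraph of the abstract also gives 15 weeks for the study.

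The Progression criteria section requires "recruitment and study completion rates > 50"% and names no denominator for the recruitment rate. Reach, the corresponding process measure, is defined in Tables 1 and 5 relative to the families approached.

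**The concern.** The conclusion of 15 weeks should follow from the flow and the two losses, and it does not appear to. The Recruitment section gives a third rate that matches neither the inputs nor the target. The 15-week figure also does two jobs: it is the period over which children are enrolled and the length of the whole study. Both can be true only if follow-up after the last enrolment takes no time.

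In most trials a loose accrual forecast is a minor matter. Here the Sample size section says that participation rate and recruitment time will inform sample size calculations for later studies, and the recruitment rate is a progression criterion. If the plan implies 8, 10 or 15 weeks depending on the section read, an observed recruitment time cannot be called faster or slower than expected. If the study did close at week 15, late entrants might lose follow-up. Itch is measured only from the third dressing change, and the acceptability interviews take place at the last one, so truncation would lower data completeness for a scheduling reason alone.

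**Working it through.** **Inputs.** Flow of 5 per week (stated as a minimum), 15% non-participation, 15% low suggestibility, target 30, stated time 15 weeks and follow-up of about 5 weeks (Sample size); 3 per week for 15 weeks (Recruitment); study length 15 weeks and enrolment from March to July 2022 (Study timeline).

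**Formulas.** Weekly yield = flow × (1 − non-participation) × (1 − low suggestibility). Weeks to target = 30 / yield. Children in 15 weeks = 15 × yield.

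**Attempt to reproduce the plan's figure.** Thirty children in 15 weeks is 30/15 = 2 per week. The other readings give:

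| Reading | Per week | Weeks to 30 | Children in 15 weeks |
|---|---|---|---|
| Losses multiplied, 5 × 0.85 × 0.85 | 3.61 | 8.3 | 54.2 |
| Losses added, 5 × (1 − 0.15 − 0.15) | 3.50 | 8.6 | 52.5 |
| Non-participation only, 5 × 0.85 | 4.25 | 7.1 | 63.8 |
| No losses | 5.00 | 6.0 | 75 |
| Recruitment section, 3 per week | 3.00 | 10.0 | 45 |
| Same, if the 3 are counted before screening, 3 × 0.85 | 2.55 | 11.8 | 38.3 |

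No reading gives 30 in 15 weeks. Because five per week is a minimum, a larger flow widens the gap.

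**What would make 15 weeks necessary.** At the stated losses the flow would have to be 2/(0.85 × 0.85) = 2.77 per week, or 2/0.70 = 2.86 if the losses are added. Either is little more than half of the stated minimum.

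**Whether 15 weeks is a margin for chance.** Assuming Poisson accrual with mean 54.2 over 15 weeks, the probability of fewer than 30 is about 0.0001. Over 10 weeks (mean 36.1) it is about 0.13. Random variation would justify some margin over 8 to 9 weeks, but 15 is far more than it requires.

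**Time frames.** Fifteen weeks of enrolment plus about 5 weeks of follow-up is about 20 weeks, not 15. On the calendar, the shortest span consistent with a March start and enrolment open until July is 31 March to 1 July: 92 days, or 13.1 weeks. A 15-week study would then leave 15 − 13.1 = 1.9 weeks for the last child.

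**Implied participation, as a conditional illustration.** Suppose exactly five present each week, all 75 are approached, and reaching 30 takes 15 weeks. The overall yield is 30/75 = 40%. If 15% of consenters screen low, consent is 30/(75 × 0.85) = 47%. If the 15% is a share of all potentially eligible children, consent is 40% + 15% = 55%. If consent is 85% as assumed, only 30/(0.85 × 0.85) = 41.5 children need be approached.

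**The case against.** The strongest defence is that the target is stated as a minimum, so 15 weeks is enough and the error is on the safe side. The study is a single-arm, descriptive feasibility study with no power calculation, and the participation rate and recruitment time carried into later trials will be the observed ones. All of that stands and limits the severity. It does not rescue the sentence, which presents 15 weeks as the time required, nor does it remove the disagreement with the Recruitment section.

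A second defence is that the duration wording is simply loose: 15 weeks is the enrolment window, and the flow diagram, which is not shown here, may set out the rest. That is plausible and agrees with the March-to-July window. The text would still need to give a total duration that includes follow-up.

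Three stronger readings are tempting but not supported:

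- **That 30 in 15 weeks means 47% participation and fails the progression criterion.** The protocol assumes 85%. The criterion has no stated denominator, and Reach uses families approached, whereas the five per week are only potentially eligible and some are removed before any approach. A different reading of the 15% exclusion gives 55%, which would pass.
- **That the plan must mean 10 weeks of enrolment plus 5 of follow-up.** Three per week for 10 weeks does give 30, but the Recruitment section states a 15-week recruitment period, and 10 weeks from even a 31 March start ends in early June, before July.
- **That children enrolled after week 10 cannot finish.** Five weeks is approximate and based on an average. The Hypnotherapeutic session section allows changes every three days, and five of those span only 4 × 3 = 12 days. Some late entrants would finish; those on weekly changes might not.

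**Conclusion.** The point holds as an internal inconsistency. On the stated inputs, 30 children need about 8 to 9 weeks and 15 weeks yields about 52 to 54. The Recruitment section implies 45, and the target over 15 weeks implies two per week. The 15-week figure cannot be both the recruitment period and the whole study when follow-up is about 5 weeks.

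The result assumes a constant flow at the stated minimum of five; it does not depend on whether the losses are multiplied or added. It should be corrected, because recruitment time and rate are outputs of this study. It is not critical: the target of 30 is not endangered and no outcome or analysis changes. The documents do not show that the study would fail its own recruitment criterion. They show only that the criterion lacks a denominator.

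**What to change.** Restate one consistent set of figures in the abstract and in the Sample size, Recruitment and Study timeline sections: weekly flow, each loss and what it is a share of, expected weekly yield, enrolment window, follow-up and total duration.

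- Either give about 8 to 9 weeks as the expected time to reach 30 on the stated inputs, with any margin identified as such, or state the lower flow or participation that makes 15 weeks necessary (about 2.8 potentially eligible children per week at the stated losses).
- If enrolment does run for 15 weeks, give a total duration of about 20 weeks.
- Say whether enrolment stops when the 30th child commences hypnotherapy.
- In Progression criteria, define the recruitment rate relative to families approached, as for Reach in Tables 1 and 5. If the 47% figure is mentioned at all, give it with its conditions and alongside the 55%.

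The cost is wording in these sections. No additional children, data or analyses are needed.
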